**Methods:**

We designed a multicenter, non-blinded, randomized trial to evaluate the efficacy of short-course therapy compared to standard-course therapy for AC management. The short-course therapy group will receive 1–3 days of intravenous (IV) antibiotic treatment after successful biliary drainage compared to 4–7 days of IV antibiotics after successful biliary drainage for the standard-course therapy group. The primary outcome is the clinical cure rate within 14 days from the endoscopic retrograde cholangiopancreatography (ERCP) procedure. Participants will be allocated to either treatment course using a minimization method in a non-blinded, randomized manner, with stratification factors including condition severity and facility. We determined that 210 participants would be required to achieve a statistical power of 90% with a one-sided significance threshold of 2.5% and a non-inferiority limit of 10%.

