### Extension of the antibiotic administration period

Extending the treatment period in AC is not mandatory, even with positive blood culture results. Several retrospective studies have shown that short-term administration of antibiotics (2–3 days) does not worsen outcomes, even in cases with positive blood cultures (16,30). In response, the Société de Pathologie Infectieuse de Langue Française (SPILF) recommends a short-term antibiotic administration period (within 3 days), even for cholangitis with bacteremia (31). However, an extension of the antibiotic administration period is permissible and recommended at the discretion of the attending physician in cases that meet any of the following criteria:Antibiotics were administered for over 72 h during the short-course therapy until the blood culture sensitivity results were known.For blood cultures positive for *Staphylococcus*, antibiotic therapy for more than 14 days is recommended, followed by a confirmatory negative blood culture (32).Recommending a change of antibiotics if the blood culture sensitivity results show that the antibiotic spectrum is inappropriate to cover the infection. The duration of treatment after changing antibiotics will be 24–72 h for the short-course therapy group and 96–168 h for the standard-course therapy group.Allowing a change or extension of antibiotics with a lack of improvement in clinical symptoms (chills, body temperature > 37.5 °C on the third day of enrollment (33), abdominal pain, or jaundice). However, antibiotic administration should be limited to a maximum of 7 days.Even if antibiotics are discontinued once, it is permissible to restart them in cases of poor drainage (if the T-bilirubin level on the third day after ERCP abnormally exceeds 80% of the level before ERCP (34)). However, antibiotic administration should be limited to a maximum of 7 days.Extending the antibiotic administration period up to 14 days, including oral administration, is permissible at the discretion of the attending physician in patients already diagnosed with artificial valve replacement surgery, previous infectious endocarditis, or congenital heart disease (single ventricle, complete transposition of the great vessels, tetralogy of Fallot) or if gram-positive coccal bacteremia is confirmed.Extending the antibiotic administration period according to concurrent infection is recommended if other infections, such as liver abscess, cholecystitis, or intra-abdominal abscess, are discovered after starting the trial. Cholecystitis and intra-abdominal abscesses should be treated for 1–4 days after appropriate source control (35–37). Evidence regarding liver abscess treatment is scarce; nevertheless, the duration of antibiotic treatment should be tailored to the patient’s condition, ranging from 8 to 69 days (38). Recommending an appropriate antibiotic administration period in cases where the source of infection cannot be controlled is difficult; nevertheless, the general recommendation is 1–2 weeks for cholecystitis and 2–6 weeks for liver abscesses.

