### Outcome measures

The primary outcome was defined as the rate of cases that achieved clinical cure within 14 days and survived without recurrence, according to the guidelines recommended by the U.S. Food and Drug Administration for complicated urinary tract infection outcomes (39). Clinical cure refers to the resolution of all pre-treatment clinical symptoms (chills, fever > 37.5 °C, abdominal pain, jaundice, impaired consciousness). Recurrence was defined as the reappearance of clinical signs suggestive of cholangitis in a case that had completed antibiotic therapy and achieved clinical cure, necessitating the resumption of antibiotic administration. Clinical signs suggestive of cholangitis recurrence include any of the following: (1) reappearance of clinical signs of cholangitis; (2) manifestation of signs of infection in the liver, pancreas, or biliary tract; or (3) other signs of infection considered related to the initial cholangitis episode (30,40).

The secondary outcomes include the following:Recurrence rate within 30 daysMortality rate within 30 daysTotal number of days of antibiotics required for both groups within 30 daysTotal number of days of hospitalization required for both groups within 30 daysClinical cure rates by severityClinical cure rates by the presence or absence of fever at the end of antibiotic treatmentClinical cure rates in older populations aged ≥ 75 years (18,41)Clinical cure rates by blood culture resultsClinical cure rates by bile culture resultsClinical cure rates based on antibiotic susceptibility before ERCPClinical cure rates based on antibiotic administration duration before ERCPClinical cure rates based on the time from admission to the ERCP procedureClinical cure rates based on AC etiologyTreatment costsIncidence of the following adverse events within 14 days:(a). Rash(b). Diarrhea (defined as ≥ 3 loose stools per day (42))(c). *C. difficile* enteritis (42), confirmed experimentally and through clinical signs

Clinical signs: Presence of diarrhea (≥ 3 formless stools within 24 h).

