### Statistical analysis

Regarding the primary endpoint, the clinical cure rate with 95% confidence intervals will be compared between the short-course therapy group (24–72 h) and the standard-course therapy group (96–168 h) in the full analysis set (FAS), which will include all registered participants who receive any part of the treatment protocol. Subgroup analyses will be conducted based on severity, age, AC etiology, and other baseline factors using the confidence intervals of the differences and logistic regression models. Interaction effects will be examined. The primary analysis population is the FAS; however, analyses using the per-protocol set (PPS), which includes participants from the FAS who had no study protocol violations and were compliant with the protocol, will also be conducted to confirm that the same conclusions are drawn from both sets.

Secondary endpoints will also be examined in both the FAS and PPS sets; these will include the following variables within 30 days: the recurrence and mortality rates, required days of antibiotic use, required days of hospitalization, and treatment costs.

A safety analysis will be conducted among the participants who received the study treatment at least once. All adverse events will be reported, and serious adverse events (SAE) will be tallied separately. Adverse events observed after administration of the trial drug will be tabulated by group, and the number of occurrences, cases, and incidence rates will be calculated and compared between groups. All adverse events will be analyzed, regardless of causality. Descriptive statistics will be calculated by group for clinical laboratory tests, and clinically significant differences will be highlighted. Other parameters will be analyzed by variable type; descriptive statistics will be calculated for continuous variables and frequencies tallied for categorical variables in each group.

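### Clinical cure ignores rescue antibiotics, and recurrence can be scored only after the course ends, so the primary endpoint does not score like events alike in the two arms

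*Protocol article*

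**What the plan says.** Protocol article, Outcome measures: the primary outcome is "the rate of cases that achieved clinical cure within 14 days and survived without recurrence". The abstract fixes the clock: "The primary outcome is the clinical cure rate within 14 days from the endoscopic retrograde cholangiopancreatography (ERCP) procedure". Cure is defined by symptoms alone: "Clinical cure refers to the resolution of all pre-treatment clinical symptoms". On recurrence: "Recurrence was defined as the reappearance of clinical signs suggestive of cholangitis in a case that had completed antibiotic therapy and achieved clinical cure"; the sentence goes on to require that antibiotics had to be resumed.

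Protocol article, Extension of the antibiotic administration period, lists permitted departures from the allocated duration. Three matter here:
- non-response: "Allowing a change or extension of antibiotics with a lack of improvement in clinical symptoms", capped at 7 days;
- poor drainage: "Even if antibiotics are discontinued once, it is permissible to restart them in cases of poor drainage", triggered by a day-3 bilirubin criterion and also capped at 7 days;
- pending cultures: antibiotics given for more than 72 h "during the short-course therapy until the blood culture sensitivity results were known".

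Protocol article, Statistical analysis: the full analysis set (FAS) is primary. The per-protocol set (PPS) is the check, "which includes participants from the FAS who had no study protocol violations and were compliant with the protocol". The planned courses are 24-72 h and 96-168 h.

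**The concern.** The Discussion asks whether 24-72 h of antibiotics is non-inferior to 96-168 h. Two features of the endpoint blur that question.

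First, a short-course patient who has not improved by day 3 may be treated into the standard-course range, recover by day 14 and be credited to the short course. This pulls the arms together, which in a non-inferiority trial favours the claim. A permitted extension is not described as a violation, so the PPS apparently keeps the same patients and would not show the effect.

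Second, recurrence can exist only once antibiotics are finished, and they finish earlier in one arm by design. The same clinical event in the first week can fail one patient and not the other. This works against the short course.

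The number of events is small: at 95% cure, about 5 failures are expected per 100 patients. A few patients scored one way or the other can change the conclusion.

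**Working it through.** **1. The plan's own figure.** Inputs (Sample size section): cure 95% in both arms, margin 10 points, one-sided 2.5%, power 90%.
n per arm = (1.960 + 1.282)² × [0.95×0.05 + 0.95×0.05] / 0.10² = 10.507 × 0.095 / 0.01 = 99.8, so 100 per arm and 200 in all. The stated size reproduces. The question is what is being counted, not this arithmetic.

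**2. The same event in the two arms**, reading the definitions as written:

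| Event | Short course | Standard course |
|---|---|---|
| Not improved on day 3, antibiotics extended or changed, resolved by day 14 | cure | cure |
| Restart for poor drainage on bilirubin, or before cure, resolved by day 14 | cure | cure |
| Signs return after completion and cure, antibiotics resumed | failure | failure |
| Signs return on about days 4-7 after initial resolution, then clear by day 14 | failure if the course has ended | not a recurrence while still on treatment |

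Counting from ERCP, the planned time in which a recurrence can be scored is 14 − 3 = 11 to 14 − 1 = 13 days for the short course, and 14 − 7 = 7 to 14 − 4 = 10 days for the standard course.

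**3. Size of the rescue effect (assumed rates; the document gives none).** Let cure be 95% in controls. Let it be 85% in the short arm if rescue were scored as failure, which is exactly at the margin. Let a share m of the 10-point excess be rescued into cures, so observed short-course cure is 0.85 + 0.10m.
Chance of declaring non-inferiority = Φ[(0.10 − (pc − pt)) / SE − 1.960], with SE = √[pc(1−pc)/100 + pt(1−pt)/100].
Example, m = 0.5: pt = 0.90, SE = √0.001375 = 0.0371, (0.10 − 0.05)/0.0371 − 1.960 = −0.61, giving 27.0%.

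| m | Normal approximation | Exact enumeration, Newcombe / Wald interval |
|---|---|---|
| 0 | 2.5% | 2.3% / 3.4% |
| 0.25 | 9.2% | 8.1% / 11.3% |
| 0.50 | 27.0% | 23.2% / 29.8% |
| 0.75 | 59.2% | 51.3% / 59.9% |
| 1 | 90.1% | 83.2% / 88.6% |

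**4. Size of the recurrence effect (assumed rates).** Let 3% fail for other reasons. Let the same true relapse rate r apply in both arms, with a share s of relapses falling while only the short arm is off treatment. Short-course cure = 0.97 − r; standard-course cure = 0.97 − r(1 − s); the spurious difference is −rs. It ranges from −0.03 × 0.25 = −0.75 points to −0.08 × 0.75 = −6.0 points. Power by the formula in step 3, at 100 per arm:

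| r | All relapses scored in both arms | s = 0.25 | s = 0.75 |
|---|---|---|---|
| 3% | 84.6% | 81.0% | 72.2% |
| 5% | 74.1% | 65.8% | 45.6% |
| 8% | 61.8% | 47.1% | 18.1% |

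This takes every standard-course patient to be on treatment throughout that interval and to resolve again by day 14, so it is towards the upper end.

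**5. How few patients matter.** With 5 failures among 100 controls, the lower 95% limit stays above −10 points with 7 short-course failures by Newcombe (−9.3) and with 8 by Wald (−9.8). It falls below with one more (−10.6 and −11.1).

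**The case against.** Several counter-arguments have force.

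- A reader might infer that any restarted antibiotic still leaves a cure. The document does not support that. A restart for returning signs after completion and cure meets the recurrence definition and is a failure. Only restarts on the bilirubin criterion, or before cure is reached, can escape.
- A reader might infer that the endpoint is biased towards non-inferiority. That is also unsupported: the recurrence rule pushes the other way, and no rescue or relapse rates are given.
- The article does not say how permitted extensions are classed for the PPS, and such detail often sits in a fuller document. That these patients stay in the PPS is an inference from its wording.
- Antibiotic days and 30-day recurrence are secondary outcomes in both sets, so heavy extension in the short arm would be visible. It would not change how the primary endpoint is scored.
- An Event Adjudication Committee is listed under Trial oversight. However, the Discussion says attending physicians assess outcomes, and no adjudication rule for rescue is shown.
- Being a few events from the threshold is true of any trial near its margin. Step 5 shows sensitivity, not bias.
- A tempting remedy is to fail anyone treated beyond the allocated window. That would itself depend on the arm: treatment to day 6 for the same day-3 fever is outside the short window and inside the standard one. With truly equal arms at 95%, failing non-responders in the short arm only cuts the exact chance of success from 83% / 89% (Newcombe / Wald) to 59% / 68% at 2% non-response, and to 25% / 32% at 5%.

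What remains is that the cure definition, read literally, does not mention antibiotics, and that the recurrence definition requires a completed course.

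**Conclusion.** The point holds in a limited form. As written, patients extended or switched for non-response, or restarted for poor drainage or before cure, can count as cures in their assigned arm. Returning signs on about days 4-7 can be scored differently by arm. These are consequences of stated rules, not of omitted detail.

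Either effect could be large enough to matter. At the margin, the false-claim rate is 9% to 27% if a quarter to a half of the excess failures are rescued. In the opposite direction, the spurious difference is 0.75 to 6.0 points. Both ranges rest wholly on assumed rates, and opposing effects of unknown size cannot be relied on to cancel. The document supports no statement about the net direction.

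A strategy of short course with rescue allowed would be a legitimate comparison, but it is not the question the Discussion states.

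**What to change.** Change the scoring only and leave the care rules alone.

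1. **Relapse.** From a common time origin (randomisation or ERCP) to day 14, in both arms and whether or not the course is complete, count as failure any reappearance of cholangitis signs after initial resolution that needs new, changed, resumed or prolonged antibiotics or repeat drainage.
2. **Rescue.** Pre-specify a sensitivity analysis in FAS and PPS, not a gate. In it, rescue for persisting or returning signs, poor drainage or new hepatobiliary infection is non-cure. Use the same clinical criterion and time point in both arms, not departure from the allocated window. Record the reason for every extension, switch or restart. Do not count those made only for pending cultures, organism, cardiac risk or unrelated infection.
3. **PPS.** State how patients extended for non-response are handled.
4. **Reconcile two passages.** The extension section allows extension for temperature above 37.5 °C on the third day, while the Discussion says duration is not altered where fever persisted. How much rescue occurs depends on which is followed.

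Cost: a protocol amendment and registry update, one data-capture field, and settling the rules before outcomes are analysed, since enrolment is under way. The sensitivity analysis will have less than the stated 90% power, and this should be said. With rescue in 2% of each arm, cure is 0.95 × 0.98 = 93.1% and power about 74-80%. With 5%, cure is 0.95 × 0.95 = 90.25% and power about 63-68%. These rates are assumed, and the ranges span Newcombe and Wald intervals at 100 per arm. Keeping 90% power by the plan's formula would take 135 or 185 per arm, which is why this analysis should inform the reading of the result and not decide it.

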Experimental confirmation:Detection of *C. difficile* toxin A and/or toxin B in stoolPositive *C. difficile* stool antigenPositive *C. difficile* cultureDetection of specific genes of *C. difficile* by molecular diagnostic methods such as polymerase chain reactionDetection of *C. difficile toxins *by the cell cytotoxicity neutralization assayDrug-induced liver injury (43), according to any of the following criteria:Hepatic dysfunction (alanine aminotransferase [ALT] elevation exceeding 5 × ULN)Alkaline phosphatase (ALP) elevation exceeding 2 × ULNALT elevation exceeding 3 × ULN, and total bilirubin concentration exceeding 2 × ULN

Additionally, drug-induced liver injury will be diagnosed if there is no observed worsening of biliary duct dilation upon re-evaluation with imaging diagnostics, or if there is a re-elevation of hepatic and biliary enzymes following an initial decrease.Acute kidney injury (44), according to any of the following criteria:An increase in serum creatinine by ≥ 0.3 mg/dL (≥ 26.5 µmol/L) within 48 h from the time of initial administration of antibiotics at the start of the trial (or from the time they were first used, if before the start of the trial)An increase in serum creatinine to ≥ 1.5 times the baseline from the time of initial administration of antibiotics at the start of the trial until the end of administration

Serum creatinine results obtained by the attending physician within this period will be included in the evaluation, even if measured on non-scheduled test days.

The baseline during normal times was defined as the creatinine value within 1 year before the start of the trial. In cases with an unknown baseline, the lowest value within 7 days before the end of antibiotic administration will be used as the baseline.

Adverse events will be graded using the Common Terminology Criteria for Adverse Events version 5.0 (45).

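### The 1.5-fold creatinine criterion for acute kidney injury, and its fallback baseline, are tied to the end of antibiotics, which is the randomised factor; both should be made common to the two arms

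*Protocol article*

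**What the plan says.** All references are to the protocol article. Outcome measures lists adverse events, AKI among them, as incidence over 14 days, and then defines the event: "Acute kidney injury (44), according to any of the following criteria". Either of two criteria is enough.

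- **Rise of at least 0.3 mg/dL:** assessed "within 48 h from the time of initial administration of antibiotics at the start of the trial", or from first use if antibiotics began before the trial.
- **Rise to at least 1.5 times baseline:** assessed "from the time of initial administration of antibiotics at the start of the trial until the end of administration".

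Other creatinine results are admitted only inside that period: "Serum creatinine results obtained by the attending physician within this period will be included in the evaluation, even if measured on non-scheduled test days".

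Two baseline rules follow. The preferred one is "The baseline during normal times was defined as the creatinine value within 1 year before the start of the trial". The fallback is "In cases with an unknown baseline, the lowest value within 7 days before the end of antibiotic administration will be used as the baseline".

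Statistical analysis gives the durations as 24–72 h and 96–168 h. It compares adverse-event incidence between groups, whatever the cause, and states no adjustment for length of observation. Assessment and follow-up places clinical assessments on the day of ERCP, the next day, at the end of antibiotics, and on days 14 and 30, in both arms.

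**The concern.** In a duration trial, an outcome observed until treatment ends is observed for a time that allocation itself sets. A 1.5-fold rise first appearing on day 4 counts in a patient still on the standard course and is outside the definition in a patient who stopped on day 2. The comparison then mixes any renal effect of duration with unequal observation time.

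The fallback baseline has a related fault. It uses values measured after randomisation, and its look-back interval moves with the arm. In the standard arm that interval usually covers more of the recovery after drainage, so the minimum may be lower and the 1.5-fold threshold easier to cross.

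What is at stake is a safety claim. The Background cites antibiotic-induced organ damage as a harm of prolonged treatment, and the Discussion anticipates fewer side effects with the short course. An AKI difference in that direction could not be read at face value under the present definition.

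**Working it through.** **The plan's own figure.** No AKI rate or AKI calculation is given. The only calculated figure is the primary sample size, which reproduces: (1.960 + 1.282)² × 2 × 0.95 × 0.05 / 0.10² = 99.8, so 100 per group. It is used below only as the number per arm.

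**1. Direction, known baseline.** Take one measured creatinine series and one prior-year baseline. If the series reaches 1.5 times baseline before the short stop, it has also done so before any later stop; the reverse does not hold. So the standard arm has as many 1.5-fold events or more. This needs no assumed rate, but it does need the same measurements in both arms. If only scheduled samples exist, the end-of-antibiotics sample falls on different days, and a transient early rise could be caught in the short arm alone.

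**2. Observation time.** Midpoints are 48 h and 132 h, and 132/48 = 2.75. The range is 96/72 = 1.33 to 168/24 = 7.0. Antibiotics may start before drainage, which occurs within 48 h of hospitalisation (Inclusion criteria). If that time counts (an assumption), the midpoint ratio is 156/72 = 2.17 with a 24 h lead-in and 180/96 = 1.88 with 48 h.

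**3. The 1.5-fold criterion alone.** Risk = 1 − exp(−h × days), with the same assumed daily hazard h in both arms, 2 versus 5.5 days, and no lead-in.

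| Assumed h per day | Short | Standard |
|---|---|---|
| 0.5% | 1.0% | 2.7% |
| 1% | 2.0% | 5.4% |
| 2% | 3.9% | 10.4% |

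**4. Both criteria.** Let c be an assumed AKI rate in the first 48 h, common to both arms, with hazard h only afterwards and a 24 h lead-in. The time beyond 48 h is 1 day (short) and 4.5 days (standard). With c = 5% and h = 1%:

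- Short: 1 − 0.95 × exp(−0.01) = 5.9%
- Standard: 1 − 0.95 × exp(−0.045) = 9.2%
- Difference: 3.2 points, with about a 14% chance of a significant result at 100 per arm (two-sided 5%)

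At h = 1%, c = 3% gives 4.0% versus 7.3%, and c = 10% gives 10.9% versus 14.0%. At c = 5% and h = 2% the result is 6.9% versus 13.2%, with a 32% chance of significance.

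**5. Fallback baseline.** The same creatinine process was simulated in both arms with no new injury, 4,000 patients per arm per scenario. All inputs are assumptions, and any value including the presentation value may count against the minimum.

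| Scenario | Short | Standard |
|---|---|---|
| Raised at admission (+0.4 on 1.0 mg/dL, recovery constant 2 days, 5% variation), daily tests | 7.2% | 30.0% |
| Same, scheduled tests only | 6.9% | 23.6% |
| Same, daily tests, known usual baseline | 25.8% | 25.7% |
| Stable creatinine, 10% variation, daily tests | 2.2% | 7.0% |
| Stable creatinine, 10% variation, scheduled tests only | 2.3% | 2.0% |

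The size depends strongly on what counts as an increase. In closely similar models (presentation median 1.2 times usual, log-SD 0.2–0.3, half-life 1.5–2 days, variation 5–6%, samples on days 0, 1 and at the end of antibiotics):

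- presentation value counted, any order: 0.1–2.4% short versus 7.7–16.3% standard
- only day-1 and end-of-treatment values set against the minimum: 0–0.8% versus 1.4–9.0%
- a true later rise required: 0.01–0.8% versus 0.1–2.5%

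**6. After the change.** With one 14-day window and equal hazards of 0.5%, 1% and 2% per day, both arms have 6.8%, 13.1% and 24.4%; the ratio is 1.00.

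**The case against.** The best case for the plan has five parts.

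- **The 48 h criterion is arm-neutral.** This stands. A reader might infer that the whole AKI definition ends with treatment, or that the standard arm must show more AKI. The text supports neither: one of two alternative criteria has a fixed window, and the inequality is as many or more. If nearly all AKI occurs in the first 48 h, the artefact is small.
- **A 48 h window that closes before allocation favours nobody.** This also stands. The window can start with pre-trial antibiotics and allocation may follow drainage by up to 24 h, but such events add the same noise to both arms.
- **The fallback is limited and its direction is not fixed.** It applies only to patients without a prior-year value, a share the article does not give. Stable creatinine with scheduled tests shows no standard-arm excess, and in long courses the 7-day look-back drops the earliest values. The larger simulated excesses count a falling presentation value as an increase, yet the 1.5-fold criterion, unlike the 48 h one, does not expressly reach back to pre-trial antibiotics.
- **An on-treatment window lies inside 14 days.** So this is not a flat contradiction. The two statements still describe different observation periods and need reconciling.
- **All adverse events are tabulated and laboratory tests summarised by group.** True, but neither repairs the definition of the named AKI outcome.

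What survives is the arm-dependent window and baseline in an outcome whose incidence is compared between groups.

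**Conclusion.** The point holds in a limited form, and the definition should be changed. The structural part (1.5-fold criterion, known baseline, same measured course) follows from the protocol's own wording without any assumed rate. The fallback baseline is arm-dependent as a matter of definition; its direction towards the standard arm is likely when creatinine falls after drainage, but not assured.

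No single size can be claimed, because the article gives no AKI hazard, no early AKI rate and no proportion without a prior-year creatinine. The illustrative gap narrows from 2.7-fold for the 1.5-fold criterion alone to about 1.6-fold (9.2/5.9) once an assumed common early rate and lead-in are included. Extensions and restarts of antibiotics, which the article permits, lengthen the window further in selected patients. The consequence is confined to one secondary safety outcome; the sample size and the primary non-inferiority analysis are untouched.

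**What to change.** 1. Assess the 1.5-fold criterion over one fixed window in both arms, namely the 14 days announced for adverse events, and state the common starting point.
2. Base the between-arm comparison on creatinine time points common to both arms. Use unscheduled values in a sensitivity analysis, since they are likelier in the arm that stays longer in hospital.
3. Where no prior-year creatinine exists, use the lowest pre-randomisation value as baseline in both arms.
4. Leave the 0.3 mg/dL criterion at its fixed 48 h. A rolling 48 h window to day 14 would depend on closely spaced tests and could bring back an arm difference.

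The cost is mainly wording, settled before any comparison by arm. There are three drawbacks. A presentation baseline may already be raised and miss some AKI, though under the same rule in both arms. A transient rise between the common time points would appear only in the sensitivity analysis. It must also be confirmed that a day-14 creatinine is scheduled: the schedule figure is not available here, and missed visits may be replaced by telephone contact. If it is not scheduled, one further blood test is needed.
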